## Abstract

**Background:**

Each year, millions of Americans receive evidence-based psychotherapies (EBPs) like cognitive behavioral therapy (CBT) for the treatment of mental and behavioral health problems. Yet, at present, there is no scalable method for evaluating the quality of psychotherapy services, leaving EBP quality and effectiveness largely unmeasured and unknown. Project AFFECT will develop and evaluate an AI-based software system to automatically estimate CBT fidelity from a recording of a CBT session. Project AFFECT is an NIMH-funded research partnership between the Penn Collaborative for CBT and Implementation Science and Lyssn.io, Inc. (“Lyssn”) a start-up developing AI-based technologies that are objective, scalable, and cost efficient, to support training, supervision, and quality assurance of EBPs. Lyssn provides HIPAA-compliant, cloud-based software for secure recording, sharing, and reviewing of therapy sessions, which includes AI-generated metrics for CBT. The proposed tool will build from and be integrated into this core platform.

**Methods:**

Phase I will work from an existing software prototype to develop a LyssnCBT user interface geared to the needs of community mental health (CMH) agencies. Core activities include a user-centered design focus group and interviews with community mental health therapists, supervisors, and administrators to inform the design and development of LyssnCBT. LyssnCBT will be evaluated for usability and implementation readiness in a final stage of Phase I. Phase II will conduct a stepped-wedge, hybrid implementation-effectiveness randomized trial (*N* = 1,875 clients) to evaluate the effectiveness of LyssnCBT to improve therapist CBT skills and client outcomes and reduce client drop-out. Analyses will also examine the hypothesized mechanism of action underlying LyssnCBT.

**Discussion:**

Successful execution will provide automated, scalable CBT fidelity feedback for the first time ever, supporting high-quality training, supervision, and quality assurance, and providing a core technology foundation that could support the quality delivery of a range of EBPs in the future.

**Trial registration:**

ClinicalTrials.gov; NCT05340738; approved 4/21/2022.

## Background

There is a mental health crisis in the United States. One out of five adults will receive a mental health diagnosis in their lifetime [1], and major depression is currently the single biggest contributor to disability globally [2]. Over the past several decades, scientists have demonstrated the efficacy and cost-effectiveness [3, 4] of treatments for mental health disorders, including psychosocial interventions such as Cognitive Behavioral Therapy (CBT) [5, 6]. Despite the billions of dollars spent to disseminate evidence-based psychotherapies (EBPs) like CBT into clinical settings [5–9], access to these effective treatments remains severely limited. Training, policy mandates, and value-based incentives have not translated to broad access to high-quality EBP care in the community [10–12]. A specific barrier to effective implementation and sustainment of psychosocial interventions is the ability to measure therapist fidelity. Proctor et al. concluded that “The foremost challenge [to disseminating EBPs] may be *measuring implementation fidelity quickly and efficiently*” ([13], p. 70; italics added). To effectively implement psychosocial interventions in community settings and capitalize on the significant investment that health systems have made in EBPs, technology is needed to scale up fidelity assessment “quickly and efficiently”.

While measurement-based care has demonstrated differences in the effectiveness of providers [14], the existing technology for evaluating therapist EBP fidelity and quality does not scale up to real-world use. Specifically, the research-based, gold-standard for assessing fidelity is behavioral coding: A session is recorded, and then this “raw data” is rated by trained human coders. Research on training and quality assurance indicates that using objective, performance-based feedback like behavioral coding can enhance and sustain therapist skills [15], and ultimately client access to EBPs such as CBT [16, 17]; without performance-based feedback or quality monitoring, the return on investment of costly implementation efforts is often lost [15, 18]. However, this process is time consuming, expensive, and at times, error prone: It is a non-starter in the vast majority of community practice settings. Accordingly, mental health services researchers utilize a variety of alternative measures, including patterns of utilization (e.g., continuity of care, the number of sessions in a specified time period after diagnosis), therapist self-reports of adherence, client-rated measures of satisfaction, or measures of clinical outcomes [19, 20]. However, these are proxies of intervention quality, distal to the content of the clinical encounter, and/or subject to self-observation bias. They are all problematic indicators of fidelity and quality. Behavioral coding provides a methodology for measuring EBP fidelity, but it is impractical at scale, forcing reliance on feasible but circumspect metrics [13, 15].

Advances in machine learning (ML) and artificial intelligence (AI) have transformed computers’ abilities to create, understand, and respond to natural language. There have been major advances in basic processes (e.g., natural language understanding), as well as consumer-facing technologies (e.g., Alexa, Siri). In addition, cloud-based computing means that any internet-connected device can access server-based computing power that can scale on-demand. *Lyssn.io*, Inc, (or Lyssn, pronounced ‘listen’) is a technology start-up deploying an array of such AI technologies to support training, supervision, and quality assurance of EBPs.

Lyssn has an established cloud-based platform which includes: a) user management and organization of sessions, clinicians, and supervisors, b) recording, playback, and annotation of audio or video data from therapy sessions; c) speech-to-text transcription, d) AI-generated fidelity and quality metrics; and e) data summaries and visualizations for feedback. Therapists and supervisors access Lyssn via a web-browser, and a therapist’s caseload of patients is shown in a dashboard. Via the web-based dashboard, therapists can record in-person or telehealth sessions or upload sessions recorded elsewhere. The session review interface enables time-linked comments directly in the video (or audio) playback, which facilitates efficient use of traditional supervision. The platform allows therapists and their supervisors to discuss a session asynchronously and immediately queue up a portion of the session to review. In addition, each session is automatically transcribed via Lyssn’s in-house, state-of-the-art speech recognition algorithms, trained on over 4,000 sessions. Lyssn’s algorithms automatically identify separate speakers and their role (i.e., client vs therapist), and the transcript is searchable and linked to the recording to support efficient review and supervision [21–23]. This supervision platform serves as a base for the AI-generated psychotherapy quality metrics.

Study team members led the foundational research that established that ML-based evaluation of psychotherapy quality is possible [24]. The Lyssn platform incorporates algorithms that automatically identify Motivational Interviewing (MI) fidelity codes from session recordings. These algorithms utilize speech and language features to identify both session-level (e.g., how empathic was the therapist in this session?) and per-utterance (e.g., open questions, affirmations, confrontations within talk-turns) MI fidelity codes. The study team has published numerous papers on machine learning applied to MI and psychotherapy common factors (e.g., therapeutic alliance, facilitative interpersonal skills; [25–48]). The proposed work will extend the AI aspects of the Lyssn platform to CBT and further develop the Lyssn user-interface to support community mental health needs and workflows.

The Lyssn MI psychotherapy quality metrics have recently been extended to CBT, building on a 15-year partnership between the Penn Collaborative and Philadelphia’s Department of Behavioral Health and Intellectual disAbillity Services (DBHIDS) to implement CBT in Philadelphia’s community mental health (CMH) system, known as the Beck Community Initiative (BCI; [49]). After an initial implementation readiness phase, intensive workshops teach CBT theory and strategies, followed by weekly group case consultation. In the 6-month consultation phase, therapists’ CBT competence is rated from recorded therapy sessions using the Cognitive Therapy Rating Scale (CTRS; [50–52]). BCI training significantly improved CBT quality [49]. Prior to training, only 2% of therapists demonstrated CBT competence, while the majority of therapists (79.6%) demonstrated competence by the end of training [53]. While mean final competence scores (*M* = 41.2) were above the criterion threshold by the certification point, there remains an opportunity to improve skills among those who have completed training, as well as those who continue to participate in BCI training. Considerable research [15] also shows that training effects wear off over time without additional support, such as performance-based feedback, but this requires ongoing and extensive efforts (i.e., CTRS coding) that are not income-generating or reimbursed by payers. Clearly, human-based fidelity coding presents a substantial challenge in the training protocol. BCI CTRS coding to date is the equivalent of a doctoral-level rater working full-time for almost 4 years, or approximately $100-$125 per session rated—more than the cost (reimbursement) of the session itself. It is expensive, a rate limiting factor for scaling up training, and does not provide for sustainability, as ongoing CTRS coding ends at 6 months post-workshop. Using technology instead of humans for feedback on CBT competence would promote scale, efficiency, sustainability, and more effective allocation of limited human training resources.

Supported by R56 MH118550, the study team demonstrated initial feasibility of using ML models to rate CBT fidelity (i.e., CTRS codes; [50]) from linguistic features using a subset of sessions from previous BCI trainings [54, 55]. In 2020, Lyssn established a data use agreement with the University of Pennsylvania for the updated corpus of recordings (*n* = 2,494) and related CTRS ratings. Using transformer-based, deep neural networks [56], Lyssn developed AI-generated models for each of the 11 CTRS codes using all 2,494 sessions (within a cross-validation framework of test and training partitions; [57, 58]). The goal is that AI-generated metrics are indistinguishable from human-generated metrics, with a benchmark of 80% of human reliability (e.g., if human reliability is 0.80 and AI predicted scores correlate with human scores at 0.75, then AI predictions are 0.75 / 0.80 or 94% of human reliability). All results are based on a 30% test set of sessions that is totally distinct from the training set where models were originally developed and fit. Results shown in Fig. 1 demonstrate very strong signal and prediction. In all but one instance (CTRS code Understanding), AI-generated predictions cross the 80% of human reliability threshold. It is worth noting that in almost all clinical research using the CTRS, reliability estimates focus exclusively on the CTRS total score [49, 59]. Using AI-generated metrics, the tools achieve 100% of human reliability on the total score and also demonstrate highly accurate individual item reliability. This published research and large-scale analyses of the Penn Collaborative’s CTRS data demonstrate feasibility for the development of a LyssnCBT tool for automated fidelity feedback. Moreover, Lyssn has a standing in-house coding team that continuously provides new validation and calibration data to assess the ongoing performance of the productive AI algorithms.

**Fig. 1 Fig1:**
[figure not shown]
Percentage agreement between AI-generated and human-generated CTRS codes

### Objectives and aims

The primary objectives of Project AFFECT (AI-Based Fidelity Feedback to Enhance CBT) are to 1) refine a LyssnCBT user interface geared to CMH clinical, supervision, and administrative workflows and needs and evaluate it for usability and implementation readiness and 2) prospectively evaluate both service and implementation outcomes using LyssnCBT for supervision and quality assurance. LyssnCBT will massively scale up evaluation and feedback capacity to support high-quality CBT in routine care settings across the US. The end goal is more therapists across the country providing higher quality CBT to the millions of Americans suffering from mental health challenges.

Project AFFECT has two phases. In Phase 1 the objective is to use an existing prototype to develop LyssnCBT for CMH settings and evaluate its usability. This will include: understanding community stakeholder needs to inform software design and functionality (Aim 1), and evaluating usability and implementation readiness of LyssnCBT with CMH therapists and supervisors in a standardized roleplay design (Aim 2). Iterative software development and preliminary system validation will ensure readiness to advance to Phase 2 testing. The objective of Phase 2 is to evaluate LyssnCBT in real-world, CMH settings. A hybrid type 2 implementation-effectiveness, stepped-wedge randomized study of LyssnCBT will evaluate improvement in CBT skill use and client outcomes with 50 therapists and 1,875 clients across 5 CMH clinics (Aim 1). In addition, the hypothesized mechanism by which LyssnCBT affects clinical outcomes will be assessed (Aim 2).

## Methods/design

### Study setting

DBHIDS is a $1 billion per year healthcare system with over 300 agencies that provide behavioral health services to the city’s 470,000 Medicaid recipients, plus thousands of uninsured and underinsured individuals [51]. To qualify for services, individuals must live in Philadelphia and earn no more than 138% of the federal poverty index. The DBHIDS client population is racially and ethnically diverse (e.g., 50.1% Black / African-American, 24.8% Latino / Hispanic, 21.4% White / Caucasian) and over 54% of clients are women. Clinics treat individuals with a broad range of mental health and substance use problems: Depression (30.6%), Substance Use / Dependence (28.9%), Bipolar / Other Mood Disorders (26.7%), Psychotic Disorders (13.3%), and Anxiety Disorders (12.8%; [60]). Additional therapists are enrolled in the BCI each year through its contracts with DBHIDS.

### Participants and procedures

For Phase 1, Project AFFECT will recruit therapists, supervisors, and administrators (*n* = 25) from within the DBHIDS network. Inclusion criteria will include being currently employed at an adult outpatient CMH program that has received CBT training and implementation support from the BCI and being able to engage in study processes in English. For Phase 2, the Project AFFECT study team will identify 5 adult outpatient CMH programs from among the BCI partner programs who agree to integrate LyssnCBT into their routine procedures. Across the 5 agencies, therapists (*n* = 50) and their supervisors will be recruited for participation. Clients from the caseloads of participating therapists will be recruited to participate, with a goal of 5 consenting clients per therapist. Median treatment length at DBHIDS programs is approximately 10 weekly sessions. Across 18 months of planned data collection (~ 75 weeks), a minimum of 1,875 clients for 50 therapists are expected (i.e., 50 therapists × 5 sessions per week × 75 weeks = 18,750 sessions, with an average of 10 sessions per client).

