#### Data analysis plan

CBT fidelity, client symptom measures (PHQ-9, GAD-7), and client drop-out will be analyzed with mixed-effects models (also called hierarchical or multilevel models; [67–70]). Mixed models are very flexible with respect to nested and imbalanced data, where the current data will contain repeated measures within clients and within therapists with varying numbers of sessions and clients. Within each individual clinic, a stepped wedge design is similar to an interrupted time series, with pre-intervention (i.e., SAU) and post-intervention (i.e., LyssnCBT) phases. To model the intervention effect, separate slopes will be examined for time by phase to capture differential changes in outcomes across the two phases. *Condition* (LyssnCBT vs SAU) will be dummy-coded, and clinics will also be included in the model as dummy-coded control variables. Analyses across the outcomes will be very similar, with the exception that client drop-out is a binary outcome, whereas a logistic mixed effects model will be used instead. The primary focus in all analyses is the main effect of *Condition* and its interaction with *Time* (during the phase since LyssnCBT started). Finally, sensitivity analyses will examine missing data. Missing data could be a function of a therapist not recording a session, or of a client not completing self-report measures. The research team will review weekly reports of anticipated recordings and assessments to prevent missing data whenever possible. No significant challenges with missing data are anticipated, though calculations have assumed 20% attrition in power analyses (see below). Mixed-effects models provide unbiased estimates in the presence of missing data as long as missing data can be assumed Missing at Random (MAR; [70]). If missing data is greater than 20% or there are other concerns about the MAR assumption, a pattern-mixture approach will be used to (potentially) non-ignorable missing data [71].

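### Phase 2 neither restricts nor accounts for therapists' BCI training stage, so any BCI training under way during the trial could be mixed into the Condition effect on CTRS

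*Protocol article*

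**What the plan says.** **Selection.** Under Participants and procedures, the Phase 2 team will "identify 5 adult outpatient CMH programs from among the BCI partner programs who agree to integrate LyssnCBT into their routine procedures". The article continues: "Across the 5 agencies, therapists (*n* = 50) and their supervisors will be recruited for participation". Phase 2 research design and methods adds a minimum clinic size of eight staff therapists. Neither section makes BCI completion a condition for a Phase 2 therapist. The only training criterion nearby belongs to Phase 1 and applies to the program, not the person: "currently employed at an adult outpatient CMH program that has received CBT training and implementation support from the BCI".

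**BCI.** The Background describes workshops followed by a six-month consultation phase with weekly group case consultation. Recorded sessions are rated by humans on the CTRS, and "ongoing CTRS coding ends at 6 months post-workshop". Competence is reported as 2% before training and 79.6% at its end. The Background sees room to improve skills "among those who have completed training, as well as those who continue to participate in BCI training". Study setting states: "Additional therapists are enrolled in the BCI each year through its contracts with DBHIDS". Potential problems and alternative strategies allows new providers or sites to be added if recruitment is slow.

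**Analysis.** The Data analysis plan models Condition with separate time slopes by phase, and "clinics will also be included in the model as dummy-coded control variables". It names no term for training stage. Services as usual (SAU) is not described with respect to BCI.

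**The concern.** BCI consultation involves performance rating on the scale that is also the primary fidelity outcome. By the article's own figures it changes that outcome a great deal. Crossover is one-way: every clinic goes from SAU to LyssnCBT. A therapist whose skill rises through BCI during the trial will therefore tend to score lower in SAU and higher in LyssnCBT, whatever LyssnCBT does. Depending on when training falls relative to the clinic's switch, the fitted Condition effect can also be pushed down.

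At stake are the CTRS Condition effect, its interaction with time, and the *a* path of the mediation analysis, which is the effect of LyssnCBT on CTRS. Any effect on PHQ-9, GAD-7 or drop-out would be indirect.

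**Working it through.** The plan gives no figure for overlap with BCI, so there is none to reproduce on this point. Its client total does reproduce (50 × 5 × 75 / 10 = 1,875) and is not in question.

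**Inputs from the article.** Five clinics; one clinic switches every two months; 18 months of data; competence 2% before and 79.6% after BCI (a gain of 77.6 points); six months of consultation.

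**Assumptions.** Switches at months 2, 4, 6, 8 and 10; a linear six-month rise and then a plateau; BCI start at month 0 or 3; no LyssnCBT effect; ten therapists per clinic; competence points as a proxy for the AI-generated CTRS score. The share of therapists in training is assumed.

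**Step 1: exposure.** SAU covers 2+4+6+8+10 = 30 of 90 clinic-months (33%). A cohort starting BCI at month 0 has 2+4+6+6+6 = 24 of its 30 training clinic-months in SAU. One starting at month 3 has 0+1+3+5+6 = 15 of 30. Both are out of proportion to 33%.

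**Step 2: model.** Least squares on noise-free clinic-month means, where clinic *c* switches at s_c:

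y = share × 77.6 × min(1, max(0, (t − start)/6))

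y is fitted by clinic dummies + β·Condition + a SAU slope + a LyssnCBT slope. The true β is 0, so the fitted β is the error.

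- Coding 1 measures both slopes in months from the clinic's own switch (t − s_c).
- Coding 2 measures the SAU slope from launch and the LyssnCBT slope from the switch.

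The article does not fix the coding.

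**Step 3: trainees spread evenly, 10% share.** Coding 1 gives +0.45 (start month 0) and +1.13 (start month 3), that is, about +0.5 to +1.1 points. Coding 2 gives about +6 for either start. Clinic plus calendar-month effects give 0.

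**Step 4: all ten therapists of one clinic in a wave.** Error in β, in points, by that clinic's switch month:

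| Model and BCI start | 2 | 4 | 6 | 8 | 10 | Mean |
|---|---|---|---|---|---|---|
| Coding 1, month 0 | +4.0 | +9.0 | +4.9 | −3.1 | −10.4 | +0.9 |
| Coding 1, month 3 | −3.5 | +8.5 | +11.1 | +4.4 | −9.1 | +2.3 |
| Calendar months, month 0 | −4.5 | +4.5 | +4.5 | 0 | −4.5 | 0 |
| Calendar months, month 3 | −17.2 | −0.5 | +8.5 | +8.5 | +0.7 | 0 |

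The range is −10.4 to +11.1 with phase slopes (coding 1) and −17.2 to +8.5 with calendar-month effects. The latter averages zero over the random order, but the trial draws only one order of five clinics.

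**Cross-check in SD units.** On a normal scale with equal SD, 2% to 79.6% is a gap of 2.88 SD. With half of one clinic's therapists training (10% of the 50) and starts at month 0, 3 or 6, coding 1 gives −0.19 to +0.20 SD and calendar-month effects give −0.42 to +0.25 SD. Error of both signs appears again. With trainees spread evenly at 10% from month 0, the change in slope between phases is also off, by −0.02 SD per month, so the Condition by Time term is affected too.

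**The case against.** **A condensed article may leave this out.** Therapist-level eligibility and covariates may stand in the full protocol or the analysis plan. No passage says that any Phase 2 therapist will be in training. The phrase about continuing trainees is Background, not an eligibility rule. This stands as a limit: the point is conditional. But the article does fix the program pool, the comparator and the main model terms, and its Methods section says BCI intake is continuing. Overlap is therefore foreseeable.

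**A stronger reading is tempting.** A reader might infer that BCI does run unequally across the phases and that the error is very large. The raw averages invite this. For trainees starting at month 0, competence is 45.1% in SAU and 77.4% in LyssnCBT (+32.3 points); for a start at month 3 the gap is +50.8. These compare phases among trainees only, without clinic or time terms. They are not what the planned model would estimate, and the phase slopes can remove much of the error when trainees are spread evenly. The documents do not establish that trainees are enrolled.

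**BCI waves may not follow clinics.** This is correct. The article describes group consultation but does not say that groups are formed by clinic. The one-clinic figures are a scenario, and an even spread with calendar-month effects leaves no error.

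**The unit is a proxy.** Also correct. The outcome is an AI-generated session score, and no analysis of the proportion competent is planned.

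**Excluding trainees would narrow a pragmatic trial.** This stands too. The article names continuing trainees among those with skills to improve, and BCI support may be part of usual services in both phases.

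**Conclusion.** The concern holds in conditional form. As written, the plan admits therapists at any BCI stage and has no term for it, so BCI training during the trial could be partly credited to, or hidden in, the Condition effect on CTRS and the mediation *a* path.

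The size is not determined by the documents. It could be nil, because the trainee share is unstated. With a modest, evenly spread share it is small under one reading of the phase slopes and several times larger under another. If training clusters in one clinic, it can reach about ten points in either direction. Calendar-month terms remove an even spread, but they balance a clinic-specific wave only on average over the random order.

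All sizes rest on the assumed share, start month, linear rise, switch months and proxy scale.

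**What to change.** In the data collection and in the CTRS and mediation models (Data analysis plan; Conceptual model and evaluation of the proposed mechanism of action):

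1. Record each therapist's BCI stage at each session date, from the Penn Collaborative's training records: not started, in workshop or consultation, or months since completion.
2. Enter it as a time-varying therapist covariate in both models.
3. Add a sensitivity analysis that excludes therapist-time inside BCI training. Keep the stage covariate in it, because a therapist with sessions both before and after training would otherwise still carry the gain from SAU into LyssnCBT.
4. Report how many therapists were in training, and when. If there were none, the matter is closed.

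The cost is a small data-linkage task and a few degrees of freedom. No eligibility restriction is needed, since it would narrow the pragmatic population.
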